### Statistical analyses

Standard parametric or non-parametric statistical tests will be employed to explore differences between females with onset of depression to those remaining symptom free. To take full advantage of the longitudinal study design, generalized mixed modelling will be employed to test whether sleep-related and other fixed or variable markers can predict the onset of perinatal depression, possibly in a time-associated manner. The evaluation of BLT effectiveness for perinatal depression should take into account that this therapy will be applied at different times during the perinatal period; therefore, this will be included as a covariate in the ANCOVA (continuous data) and logistic regression analyses (dichotomous data, proportions). Regarding the efficacy of BLT in prevention of post-partum depression we will use logistic regression analysis to compare incidence rates between the group of not-depressed patients who received light therapy during pregnancy versus untreated subjects. For all analyses *p* values < 0.05 will be considered significant. The statistical analysis will be performed using a dedicated software (SPSS, IL, USA).

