## Background

Perinatal depression (PND) refers to the onset of major depression during pregnancy (antenatal depression, AD) and up to 12 months after delivery (postpartum depression, PPD). The estimated prevalence of PND is roughly 12 % [1] with a three-fold increase in incidence of depression during the postpartum period compared to nullipara [2]. Up to 80 % of women in the postpartum period report some kind of depressive symptoms, which range from a mild and transient form of sadness that is frequently termed “baby blues” to full diagnoses of major depression [3]. The Diagnostic and Statistical Manual of Mental Disorders, 4th edition text-revised (DSM-IV-TR) defined a specific subtype of major depressive disorder as post-partum depression (PPD) when the onset of the depressive episode occurs within 4 weeks after delivery [4]. Indeed, the risk of depression in puerperal women remains high through the first postpartum year [5], and in around 50 % of the cases the onset of depression occurs already during pregnancy. Based on this, the above mentioned, wider definition of perinatal depression (PND) has been adopted. The revised fifth edition of DSM (DSM-V) does not recognise this entity as a separate diagnosis, but as a specifier of major depression by using the term of “perinatal-onset or peripartum”, where a woman has to meet the criteria for major depressive episode with an onset in pregnancy or within 4 weeks of delivery [6]. An unrecognized or an untreated PND increases the risk of preterm delivery [7], smoking and substance use, shortening of breastfeeding [8], abusive behaviour toward children, suicide [9], negative effects on the relationship with the partner and cognitive problems in infants [10]. A significantly higher mean mother-infant daily cost was estimated by the British health system for women with PND compared to women without PND [11]. The absence of defined objective markers for PND diagnosis, which is purely based on the clinical interview and therefore examiner-dependent, is a significant limit to unequivocal and early recognition of the disease. Moreover, to date, except for a history of depression or positive familiar psychiatric history, no certain medical risk factors are known to predict PND [12]. With the exception of theoretical abnormalities in hypothalamic-pituitary-adrenal axis activity and possible genetic risk factors that are shared with a variety of psychiatric disorders, the etiopathogenesis of PND is still unknown. Once PND is recognized, no definitely safe pharmacologic treatments are available during pregnancy and breastfeeding [13], and the concurrent lack of preventive therapies exposes the health of women and children to the PND related risks. Placebo-controlled, randomized trials of antidepressant substances in this population are lacking, and the methodological flaws of available studies limit the generalizability of the findings. A large meta-analysis recently concluded that evidence over benefits/harms of available compounds cannot adequately support informed decisions about the treatment of PND [14]. Furthermore, teratogenicity concerns commonly influence women’s acceptance of potentially effective treatments. Therefore, a safe and effective treatment remains an urgent, currently unmet, clinical need.

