### Specific aims

#### Primary aim

To systematically and prospectively explore sleep and sleep-related parameters, as well as mood changes during pregnancy and the postpartum in order to identify reliable, potential early diagnostic markers of PND (Life-ON study).

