### Determination of sample size

This prospective, longitudinal cohort study will include 500 pregnant females. Given that we consecutively include participants, we judge this sample size as sufficient to generate estimates for the prevalence of perinatal depression, sleep disturbances, and sleep disorders during pregnancy and postpartum. Based on a meta-analysis of prevalence and incidence studies we expect the cumulative incidence of minor and major depression during late pregnancy and postpartum to be at least 20 % (*n* = 100). Taking into consideration that we plan to include 80 females in a trial of light treatment for the prevention of postpartum depression, we expect that approximately 300 females will be symptom free, while 100 to 150 females will experience minor or major depression during the perinatal period. For the study of risk factors involved into the development of perinatal depression, our sample size will enable the detection of small to moderate effects (d > 0.3) with an adequate statistical power (≥80 %).

For the Life-ON study no significance threshold a priori is considered.

The main outcomes of Life-ON 2 will be the change of depressive symptoms, response and remission rates after 6-week bright light treatment versus placebo. Based on a previous meta-analysis we expect that the prevalence of depression during the perinatal period will be at least 25 %, which would qualify 125 participants for inclusion in the treatment trial. From our previous experiences we anticipate an attrition rate of 25 % for reasons of refusal, non-compliance, or necessity for additional/alternative treatment. A conservative estimate would, therefore, be that 80 females will complete the treatment trial. At the same time, weekly monitoring is expected to increase compliance and reduce attrition and the available data suggests that prolongation of the treatment duration to 6 weeks will increase the bright light versus placebo difference. Our conservatively planned sample size (40 versus 40) will enable us to demonstrate medium effects (d >0.56) with a one-side error level of 0.05 and adequate statistical power (≥80 %).

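### The primary aim is diagnostic markers, but the stated tests and sizing target for it concern association, and a marker at the sizing effect (d = 0.3) hardly separates cases from non-cases

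*Protocol article*

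**What the plan says.** The protocol article's Primary aim section says that sleep and mood will be explored "in order to identify reliable, potential early diagnostic markers of PND". The Life-ON design section repeats this as the expected outcome, and the working hypothesis speaks of early identification of women who will develop perinatal depression (PND).

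The Statistical analyses section names two analyses for this aim. The first is "Standard parametric or non-parametric statistical tests will be employed to explore differences between females with onset of depression to those remaining symptom free". The second is that "generalized mixed modelling will be employed to test whether sleep-related and other fixed or variable markers can predict the onset of perinatal depression". The section closes with a rule covering all analyses: p "values < 0.05 will be considered significant".

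Under Determination of sample size, the risk-factor part is justified by the claim that "our sample size will enable the detection of small to moderate effects (d > 0.3") with at least 80 % power. About 300 women are expected to stay symptom free and 100 to 150 to become depressed. The same section then states: "For the Life-ON study no significance threshold a priori is considered".

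The Background says that "except for a history of depression or positive familiar psychiatric history, no certain medical risk factors are known to predict PND".

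**The concern.** A diagnostic or early-identification aim asks how well a marker tells apart, woman by woman, those who will and will not become depressed. A group-difference test or a model coefficient asks whether the association is zero. The second question can be answered yes with near certainty while the answer to the first is poor, and the effect the cohort is sized for lies in that region.

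There is also the question of added value. Prior depression and family psychiatric history are named as existing predictors. Table 2 excludes only recent (under 6 months) or current major depression, so women with earlier episodes can enter. A sleep variable could reach significance because it tracks earlier depression.

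The Abstract and the Discussion tie the results to preventive medical and social strategies. If significance were read as diagnostic value, those strategies could be built on variables that barely discriminate.

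**Working it through.** **Inputs from Determination of sample size:** d = 0.3 as the boundary effect; 100 to 150 cases; about 300 symptom-free women; power of at least 80 %; incidence of at least 20 % (Life-ON) or at least 25 % (Life-ON 2).

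**Assumptions:** a marker that is normal with equal variance in both groups, and a test of two means. The article names neither a t test nor a sidedness for Life-ON. Both sidednesses are shown, because Life-ON 2 is planned "with a one-side error level of 0.05".

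**Step 1: the plan's own power figure.** Power ≈ Φ(d·√(n₁n₂/(n₁+n₂)) − z), with z = 1.960 (two-sided 0.05) or 1.645 (one-sided 0.05).

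| Cases vs non-cases | d·√(n₁n₂/(n₁+n₂)) | Two-sided | One-sided |
|---|---|---|---|
| 100 vs 300 | 0.3 × 8.660 = 2.598 | 73.8 % | 83.0 % |
| 125 vs 300 | 0.3 × 9.393 = 2.818 | 80.5 % | 88.0 % |
| 150 vs 300 | 0.3 × 10.000 = 3.000 | 85.1 % | 91.2 % |

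The noncentral t agrees to within 0.2 percentage points. The claim of at least 80 % is met throughout if one-sided, and from about 125 cases if two-sided. The sizing claim is therefore reproducible.

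**Step 2: what d = 0.3 means for discrimination.**
- AUC = Φ(d/√2) = Φ(0.212) = 0.584.
- Sensitivity at 90 % specificity = Φ(d − 1.2816) = Φ(−0.982) = 16.3 %, so about 84 % of cases are missed.
- Positive predictive value at 20 % incidence = 0.163 × 0.20 / (0.163 × 0.20 + 0.10 × 0.80) = 0.0326 / 0.1126 = 29 %. At 25 % incidence it is 0.0408 / 0.1158 = 35 %.
- At the best single cut, sensitivity = specificity = Φ(0.15) = 56 %.

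**Step 3: the smallest observed difference that is significant.** Two-sided, d = 1.96·√(1/n₁ + 1/n₂). This is 0.23 for 100 vs 300 (AUC 0.56) and 0.20 for 150 vs 300 (AUC 0.555).

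**Step 4: for comparison.** An AUC of 0.70 would need d = √2 × Φ⁻¹(0.70) = 1.414 × 0.524 = 0.74, well above the sizing target. The value 0.70 is only illustrative; the article sets no accuracy bar.

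**Step 5: the threshold statements.** Statistical analyses applies p < 0.05 to all analyses. Determination of sample size says that Life-ON has no a priori threshold. On the first reading the only criterion is one of association; on the second there is no stated criterion.

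**The case against.** The strongest reply is that the analyses fit the study's own framing. The Null hypothesis section is worded as no relation between sleep features and PND. The Abstract gives the primary aim as exploring and characterising risk factors, and the sample-size text also speaks of risk factors. For that aim, association tests are appropriate. The aim says potential markers and the group tests are there to explore. This stands as far as it goes, but the aim also says reliable and diagnostic, and the mixed model is meant to test prediction.

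A reader might infer that the plan will recognise a diagnostic marker by p < 0.05 alone. The article does not support that: no sentence says so, and the no-threshold statement for Life-ON points the other way. A reader might also infer that the study cannot identify who will become depressed. That does not follow either. The figures describe one marker at the lower edge of d > 0.3; a stronger marker, or several combined, could do better.

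The article does not say that known predictors will be ignored. The mixed model's other fixed markers could include them, and covariate choice is ordinary analysis-plan content. Accuracy measures may likewise sit in a full protocol or analysis plan that is not shown, so their absence is not itself the finding. What remains is the mismatch between the stated aim and the stated criterion and sizing target, together with the contradictory threshold.

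**Conclusion.** The concern holds in a limited form. The diagnostic aim is matched only with analyses of association and an association-sized effect, and the one significance criterion is stated inconsistently. A marker at the sizing effect would be significant in 74–85 % of studies (two-sided) or 83–91 % (one-sided) while having an AUC of 0.58 and finding 16 % of cases at 90 % specificity. Significance under this plan cannot by itself support the term reliable diagnostic marker.

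The accuracy figures rest on the equal-variance normal model and a single marker; the significance rates also rest on a comparison of two means and the plan's expected group sizes. This is a matter of analysis and wording that should be put right. It is not a fault in the cohort design, and the association analyses remain valid for the risk-factor aim.

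**What to change.** 1. Reconcile the two threshold statements for Life-ON, and state the sidedness of whatever threshold is kept.
2. State that a significant group difference or model coefficient shows association only.
3. For the diagnostic aim, report the AUC of the sleep markers corrected for optimism by bootstrap or cross-validation. Report its gain, with a 95 % confidence interval, over a reference model of prior depression and inclusion EPDS. Add family psychiatric history if it is collected; the article does not list it among the items recorded. Also report sensitivity and positive predictive value at a fixed specificity.
4. Base any conclusion that a variable is a diagnostic marker on the size and precision of these measures. Neither a p value nor an AUC-gain interval that merely excludes zero is enough, since the latter is again a test against zero and a trivial gain could pass it.

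No extra participants are needed to estimate accuracy usefully. At a true AUC of 0.70, the Hanley–McNeil 95 % half-width is about 0.06 with 100 vs 300 and 0.05 with 150 vs 300, before any optimism correction. The cost is a little more analysis and some rewording. The downside is that fewer variables will be called diagnostic markers.

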### Experimental design – Life-ON study

Life-ON is an observational, longitudinal study, which will systematically and prospectively explore sleep and sleep-related parameters during pregnancy and their correlation with the onset of PND. The expected outcome is to identify reliable, potential, early diagnostic markers of PND.

Demographic and gynaecological/obstetrical data will be collected for all women included in the study. Mood, sleep quality and disorders, and other biomarkers will be assessed at regular intervals during the perinatal period, until 12 months postpartum, in all participants (Additional file 1: Table S1a).

Sleep investigations will include an interview with a sleep expert to determine lifetime and current sleep disturbances, supplemented with questionnaires assessing sleep quality, insomnia, daytime sleepiness, circadian chronotype, sleep-related movement disorders and parasomnias. Unattended ambulatory polysomnography (PSG) will be conducted in all participants between the 23th and 25th gestational week. This will include electroencephalogram (F3, C3,O1 referenced to the contralateral mastoid, M2), bilateral electro-oculogram, surface electromyogram of submentalis muscle and bilateral tibialis anterior muscles, electrocardiogram and sleep respiratory parameters (nasal air flow, thoracic and abdominal respiratory effort, oxygen saturation).

Sleep will be scored by a sleep specialist according to the international guidelines [52]. The rest/activity cycles during pregnancy and postpartum will be assessed by 7-days actigraphic recordings repeated for 3 times: between the 23th and 25th gestational week, around the 3rd (between 90 and 105 days) and between the 11th and the 12th month after delivery.

All participants will undergo a psychiatric and psychological evaluation, including semi-structured interviews and questionnaires for screening depression, stressful life events and selected personality traits. Depressive symptoms will be assessed at the time of study inclusion and approximately every 3 months until the 12th month postpartum with a higher sampling rate (every two weeks) during the two postpartum months; the diagnosis of PND will be always established using structured clinical interviews conducted by staff psychologists/psychiatrists.

### Experimental design – substudy Life-ON 1

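### The risk-factor analysis does not require the PSG or actigraphy recording to precede onset of depression, so a consequence of depression can be read as an early marker

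*Protocol article*

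**What the plan says.** All places are in the protocol article.

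- **Specific aims:** the primary aim is to find potential early diagnostic markers of perinatal depression from sleep, sleep-related and mood data.
- **Statistical analyses:** standard tests will "explore differences between females with onset of depression to those remaining symptom free". A generalized mixed model will then test whether markers "can predict the onset of perinatal depression, possibly in a time-associated manner".
- **Experimental design – Life-ON study:** "Unattended ambulatory polysomnography (PSG) will be conducted in all participants between the 23th and 25th gestational week". Actigraphy is recorded in the same window and again "around the 3rd (between 90 and 105 days) and between the 11th and the 12th month after delivery". More generally, "Mood, sleep quality and disorders, and other biomarkers will be assessed at regular intervals during the perinatal period"; that schedule is in a supplement that is not shown.
- **Table 2:** women enter at 10-15 weeks, and depression is an exclusion only at inclusion.
- **Background:** in around 50% "of the cases the onset of depression occurs already during pregnancy".
- **Determination of sample size:** 100 to 150 cases and about 300 symptom-free women are expected, with at least 80% power for d > 0.3.

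**The concern.** An early marker has to be present before the illness it predicts. The group comparison makes a woman a case without reference to whether onset came before or after her recording. A woman who becomes depressed at week 18 has her PSG at weeks 23-25, possibly while depressed, and still counts as a case whose sleep is compared with that of healthy women.

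The Background section on sleep, chronobiology and depression itself lists the PSG changes seen in depressed patients: longer sleep latency, more wake after sleep onset, less slow-wave sleep, shorter REM latency. If some cases carry those changes because they are already ill, the comparison can show a difference when sleep has no predictive value. The postpartum actigraphies are more exposed still, because they follow many onsets. At stake is the central claim that sleep in pregnancy identifies women who will later become depressed.

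**Working it through.** **1. The plan's own figure.** With unit SD, power at d = 0.3 is Φ(0.3/SE − z), where SE = √(1/cases + 1/300). At 100 cases SE = 0.1155 and 0.3/SE = 2.598, giving 83.0% one-sided and 73.8% two-sided at 5%. At 150 cases it is 91.2% and 85.1%. The stated figure therefore reproduces one-sided over the whole range, and two-sided from about 125 cases (80.5%). The article gives no sidedness for Life-ON, so both are shown.

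**2. Gap between entry and recording.** Shortest 23 − 15 = 8 weeks, longest 25 − 10 = 15 weeks.

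**3. Share of cases with onset before week 24.** The documents give only the 50% for all of pregnancy. Assuming even onset within pregnancy:
- All antenatal onsets placed in weeks 12-40: 0.5 × (24 − 12)/(40 − 12) = 0.21.
- Onsets spread over weeks 0-40 (0.0125 per week), those before entry removed. Entry at week 12: 0.15/0.85 = 0.18. Entry at week 15: 0.1125/0.8125 = 0.14.

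The range is about 14-21%.

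**4. Spurious effect.** Suppose there is no true predictive effect, a share q of cases is already depressed at the recording, and depression shifts the marker by s SD (assumed 0.5-0.8; not in the documents). Then apparent d = q × s.

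| q | s | apparent d | d/SE (100 vs 300) | two-sided rejection at 5% |
|---|---|---|---|---|
| 0.10 | 0.3 | 0.03 | 0.26 | 6% |
| 0.14 | 0.5 | 0.07 | 0.61 | 9% |
| 0.18 | 0.5 | 0.09 | 0.78 | 12% |
| 0.21 | 0.5 | 0.105 | 0.91 | 15% |
| 0.21 | 0.8 | 0.168 | 1.46 | 31% |

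The first row shows that a small share with a small shift does almost nothing.

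**5. Later actigraphy.** By 3 months postpartum every antenatal onset has already happened. On the same assumptions that is between (0.5 − 0.1875)/0.8125 = 38% and 50% of cases, before any postpartum onset is counted. By months 11-12 nearly the whole onset window has passed.

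**6. Light treatment.** Life-ON 3 light is given in the third trimester, after the weeks 23-25 recordings, so it cannot alter them. It may alter who becomes a case. On the article's own 20% versus 5%, that is 80 × (0.20 − 0.05) = 12 women, or 12/500 = 2.4% of the cohort.

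**7. Power after requiring the recording to come first (d = 0.3, 300 symptom-free women).**

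| cases left | one-sided | two-sided |
|---|---|---|
| 90 of 100 | 80.3% | 70.4% |
| 75 of 100 | 75.1% | 64.2% |
| 135 of 150 | 89.4% | 82.5% |

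**The case against.** The best defence is that the group test is described as exploratory and is nowhere named primary. The predictive question belongs to the mixed model in the next sentence, and a model said to predict onset from time-varying markers suggests temporal order. A condensed article may leave risk-set rules to the analysis plan. The sample-size section also takes its 100 cases from incidence in late pregnancy and postpartum, largely after the recording.

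Part of this stands. It would be wrong to infer that the group comparison is the primary analysis. The case definition is ambiguous, since the same section then speaks of the whole perinatal period. But the mixed model is time-associated only as a possibility. And because PSG is recorded once, repeated-measures modelling cannot by itself separate pre-onset from post-onset recordings. The point is not absent detail: the comparison as stated does not match the aim.

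Other stronger readings also fail:
- **That all sleep data come at weeks 23-25 or later.** This is shown only for PSG and actigraphy; interviews and questionnaires may start at inclusion.
- **That light treatment creates false predictors at weeks 23-25.** Life-ON 3 light comes later and is randomised, so it is independent of those markers and can only dilute their associations. The sample-size text also appears to set the treated women apart: "Taking into consideration that we plan to include 80 females in a trial of light treatment for the prevention of postpartum depression". A Life-ON 2 woman could receive light before her PSG only if her depression was identified before it, and a landmark removes her.
- **That blood markers need the same rule.** The only blood sample dated to weeks 23-25 is the genetic test, and depression does not change a genotype.

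**Conclusion.** The concern holds for PSG and actigraphy. As written, nothing prevents a recording made during or after depression from counting as an early marker. On the assumptions of even onset (14-21% of cases before week 24), a concurrent shift of 0.5-0.8 SD, every earlier case still affected at the recording and no true effect, the spurious d is about 0.07-0.17. The false-positive rate per marker is then about 9-31% instead of 5% at 100 versus 300.

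A reader might take a 30% share with a 0.8 SD shift and reach d = 0.24 and about 55% rejection. That needs the top of two assumed ranges at once, and the documents support neither. At the low end the bias is negligible. The ordering problem follows from the text; its size does not. The light-treatment issue is secondary and concerns later case status in about 12 women.

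**What to change.** State in the analysis section that a marker must be recorded before onset:

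1. **PSG and first actigraphy:** set a landmark at the recording. Analyse only women free of depression then, with later onset as the outcome.
2. **Repeated sleep markers, including postpartum actigraphy:** use only values from visits before the visit at which onset is detected. Mood is assessed about every 3 months for most of follow-up, and exact onset dates are not stated to be collected, so the rule should work by visit.
3. **All-cases comparison:** keep it, labelled as cross-sectional association.
4. **Germline genotypes:** exempt them; no landmark is needed.
5. **Secondary:** include randomised Life-ON 3 allocation as a covariate in the risk-factor model.

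No new measurements are needed. The cost is fewer cases, so power for d = 0.3 should be restated with its sidedness. That requires settling which threshold applies, because the sample-size section sets none for Life-ON while the analysis section applies p < 0.05 to all analyses. From 100 cases, two-sided power is 73.8% before the change, 70.4% with 90 left and 64.2% with 75 left.

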Life-ON 1 substudy consists in a genetic test on a blood sample taken during the 23rd-25th gestational week, with the aim to identify possible specific genetic polymorphisms, that may be associated with PND. Part of the blood samples taken at inclusion will be processed and stored in a bio-bank for future use.

### Experimental design – substudy Life-ON 2

Life-ON 2 is a longitudinal and interventional trial, which will investigate the effectiveness of BLT in treating PND. Women with minor or major depression, diagnosed by a psychiatric interview or with an EPDS score >12 at any time from study inclusion to 9 months postpartum, will be invited to participate in the randomized-controlled BLT trial. Participants will be randomised on a 1:1 basis to receive 6 weeks of morning BLT or dim light placebo. The trial will be single blind. Subjects will be asked to maintain their habitual bedtime and wake-up schedule, and to begin the light treatment within 20 min of habitual wake-up time. Subjects will be instructed to sit in front of the light box (Philips Energy Up HF 3419) at a specified distance (around 30 cm) and to receive an active light dose (10’000 lux) or placebo dim light (50 lux) for ½ hour. Safety will be monitored with the self-report version of the Systematic Assessment of Treatment Emergent Effects (SAFTEE). Similarly to Life-ON, all participants will be followed up until 12 months postpartum.

### Experimental design – substudy Life-ON 3

Life-ON 3 is a longitudinal and interventional trial, in non-depressed women, which will investigate the effectiveness of BLT during pregnancy in preventing PND. A subsample of 80 subjects without depression will be randomly, consecutively recruited to receive 6-week open-label BLT during the third trimester of pregnancy. The selected participants will receive ½ hour of morning BLT (10’000 lux, Philips Energy Up HF 3419) for 6 weeks. Subjects will be asked to maintain their habitual bedtime and wake-up schedule, and BLT is planned to commence within 20 min of habitual wake-up time. Safety will be monitored with the Systematic Assessment of Treatment Emergent Effects (SAFTEE). All participants will be followed-up until 12 months postpartum and the main outcome will be the incidence of postpartum depression in subjects receiving BLT compared to subjects with no treatment.

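### The Life-ON 2 models name treatment timing as their only covariate and do not mention the baseline depression score, so a literal reading gives up precision the trial could have almost for free

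*Protocol article*

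**What the plan says.** The only model description for Life-ON 2 is in the protocol article, section Statistical analyses. It states that the evaluation "should take into account that this therapy will be applied at different times during the perinatal period", and continues: "therefore, this will be included as a covariate in the ANCOVA (continuous data) and logistic regression analyses (dichotomous data, proportions". Timing is the one covariate named, and a reason is given for it. The section neither includes nor excludes a pre-treatment depression score.

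Two other places bear on this. Determination of sample size defines the outcomes: "The main outcomes of Life-ON 2 will be the change of depressive symptoms, response and remission rates after 6-week bright light treatment versus placebo". Experimental design – substudy Life-ON 2 sets the entry rule: "Women with minor or major depression, diagnosed by a psychiatric interview or with an EPDS score >12". Allocation is 1:1. The sample size section plans 40 versus 40 completers to detect d above 0.56 at a one-sided 5 % level with at least 80 % power, and it mentions no covariate adjustment.

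**The concern.** Change cannot be computed without a pre-treatment score, so the trial must hold one for every woman whose change is analysed. Entry severity is mixed, so that score is likely to carry information about the week-6 score. A model with arm and timing only, fitted to change, implicitly fixes the slope on baseline at 1 instead of estimating it. Whenever the true slope differs from 1, this leaves avoidable noise in the treatment comparison.

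At stake is the precision of a small randomised comparison of 40 versus 40. Covariates are also best fixed before the data are seen. If baseline is added later because the published text was silent, the choice is open to question in a trial where it could move a result across p < 0.05.

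**Working it through.** **Inputs from the protocol article.** 40 per arm, d = 0.56, one-sided alpha 0.05, power at least 80 % (Determination of sample size). Outcome: change in symptoms. Named covariate: timing.

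**Inputs not in the documents, assumed.** The baseline to week-6 correlation r, taken as 0.3, 0.5 and 0.7. The ratio k = baseline SD / week-6 SD, taken as 1 and then 0.7. Here d = 0.56 is read in units of the SD of the analysed change score. The small role of timing in the variance is ignored.

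**Step 1: reproduce the plan's figure.** By the normal approximation, n per arm = 2 × 2.4865² / 0.56² = 39.4, rounded up to 40. Power with 40 per arm is 80.5 % (normal) or 79.9 % (noncentral t). The stated size is therefore a plain two-group calculation with no covariate, and it holds.

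**Step 2: variance with and without baseline, week-6 SD set to 1.**
- Unadjusted change: 1 + k² − 2rk
- ANCOVA with baseline: 1 − r²
- Ratio: (1 − r²) / (1 + k² − 2rk)

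The difference between the two variances is (k − r)², which is never negative. In large samples, then, baseline adjustment cannot lose precision against unadjusted change. With k = 1 the ratio simplifies to (1 + r)/2.

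**Step 3: equal SDs (k = 1).** Power is by noncentral t, with d divided by the square root of the ratio.

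| r | Variance ratio | Reduction | 80 women act like | One-sided power, 40 vs 40 |
|---|---|---|---|---|
| no baseline | 1.00 | – | 80 | 79.9 % |
| 0.3 | 0.65 | 35 % | 80/0.65 = 123 | 92.4 % |
| 0.5 | 0.75 | 25 % | 80/0.75 = 107 | 88.9 % |
| 0.7 | 0.85 | 15 % | 80/0.85 = 94 | 85.3 % |

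**Step 4: narrower baseline (k = 0.7).** The entry rule puts a floor under severity, so the baseline spread may be smaller than the week-6 spread.
- r = 0.3: 0.91 / 1.07 = 0.85, reduction 15 %
- r = 0.5: 0.75 / 0.79 = 0.95, reduction 5 %
- r = 0.7: 0.51 / 0.51 = 1.00, no reduction

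A baseline SD larger than the week-6 SD would move the gain the other way.

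**Step 5: chance imbalance.** With 40 per arm, the difference in baseline means has a standard error of √(2/40) = 0.224 SD. A difference above 0.25 SD in either direction therefore arises in 2(1 − Φ(0.25/0.224)) = 26 % of trials. With equal SDs, it shifts an unadjusted change comparison by (1 − r) times its size in the trial where it occurs. That shift averages to zero over randomisations and is already part of the variance in Steps 2 to 4, so it is not a further loss.

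**Step 6: response and remission.** The documents give no expected rates for either outcome, and the variance formula above does not carry over to logistic regression. No figure can be given.

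**The case against.** The strongest reply is that the article says timing enters as a covariate, not as the only one. The sentence explains one design-specific addition, and a condensed article may leave the full covariate list to the full protocol or the analysis plan, neither of which is shown. Analysts also often take an ANCOVA of change to include baseline by default. This stands as far as it goes: the text is silent on baseline, and a reader who infers that the trial has decided to leave it out goes beyond the documents. It does not dispose of the point. The article chose to specify the model and to justify its covariate, and the covariate it identifies for the ANCOVA is timing, so the label alone does not bring baseline in.

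The second reply is that no stated figure fails. That is correct (Step 1). A reader might infer that the trial is underpowered or that its estimate is biased. Neither follows: the sample size was computed without covariates, and 1:1 randomisation keeps the comparison unbiased with or without baseline.

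The third reply is that the size of the gain depends on a correlation and SDs that the documents do not give. This also stands. The gain can be anything from nil to about a third of the variance over the ranges shown, so the documents do not support an unqualified statement that a large share of precision is lost.

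**Conclusion.** The point holds as a modest, worthwhile improvement to a stated model. Read literally, the Life-ON 2 analysis adjusts for timing and not for baseline severity, and so forgoes precision on the change outcome. The variance reduction forgone is 35 to 15 % for r from 0.3 to 0.7 with equal SDs (one-sided power from about 80 % to 92 to 85 %), and 15 to 0 % if the baseline SD is about 0.7 of the week-6 SD. These figures rest on assumed r and k, on an unadjusted change score as the comparator, and on d = 0.56 being in units of the SD of change. For response and remission the direction of the advice is the same, but its size is unknown.

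**What to change.** In Statistical analyses, state that for Life-ON 2 the 6-week score (or equivalently the change) is analysed by ANCOVA with arm, baseline score of the same scale and timing of treatment, and that the logistic models for response and remission use the same covariates. If the full protocol or analysis plan already says so, the sentence only brings the article into line with it. The cost is one sentence and one degree of freedom per model. No new data are needed, and the planned 40 versus 40 need not change.
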